#### Data collection overview

Clinical/research nurses, dentists and dental hygienists at each site are responsible for the data collection. Data are collected from all participants at baseline, 6 months after the end of treatment (randomisation and start of intervention), and 1, 2 and 3 years after randomisation. Non-adherence and non-retention are registered.

Data gathered through history taking or medical records include, e.g., demographics (sex, age and education), as well as information on diagnosis and treatment (tumour site and stage, treatment modality, comorbidities and medication), work ability and sick leave, eating ability, and habits, including use of nicotine and alcohol, nutritional status (anthropometrics, body composition). Body composition measurements using calf circumference are performed on all participants. Bioelectrical impedance analysis (Bodystat^®^ Multiscan 5000) is used on a subgroup.

In addition, participants complete questionnaires (PROMs) to assess HRQoL, depression, anxiety and stress, health status, self-efficacy, and self-rated oral health (Table 1). The questionnaires are completed digitally or on paper.

**Table 1 Tab1:** Data overview from patient-reported outcome measures, PROMs

Questionnaire	Description
European Organization for Research and Treatment of Cancer Quality of Life Questionnaire-Core 30 (EORTC-C30) [26]	Assesses health-related quality of life in cancer patients. Comprises 30 items covering, e.g., global health status, functional domains (physical, role, emotional, cognitive, and social), symptom scales (fatigue, pain, nausea/vomiting).
EORTC-Head and Neck Cancer Module (EORTC-HN43) [27]	Assesses health-related quality of life in patients with head and neck cancer, an updated version of HN35. Includes 43 items addressing disease- and treatment-specific issues, such as swallowing, speech, senses (taste and smell), pain, social eating, sexuality, and body image, as well as symptoms such as dry mouth and sticky saliva.
Depression Anxiety Stress Scale-21 (DASS-21) [28]	Measures negative emotional states. Consists of 21 items divided into three subscales assessing symptoms of depression, anxiety, and stress.
EQ-5D-3 L [29, 30]	Measures general health status. Consists of five dimensions (mobility, self-care, usual activities, pain/discomfort, and anxiety/depression). Each dimension has three levels of severity.
General Self-Efficacy (GSE) [31]	Assesses an individual’s perceived ability to cope with a variety of demanding situations. Consists of 10 items measuring self-belief related to problem-solving and adaptation.
Self-Perceived Oral Health (SPOH) [32]	A modified version of the SPOH instrument is used to assess subjective oral health. The instrument includes items on self-rated oral health (12 items), oral health behaviours (8 items), perceived oral health knowledge (4 items), and future perspectives (2 items).

Data on oral health (number of remaining teeth, maximum interincisal opening [MIO], caries and periodontal status) are collected during clinical examination. Participants are asked how often they have sought dental care. Computed Tomography (CT) and Cone-Beam Computed Tomography (CBCT) are used to detect pathological changes in the jaw (osteoradionecrosis). Blood and saliva samples are collected for analysis and long-term storage (biobanking). Blood samples are analysed for haematology and immune parameters, including markers of inflammation. The stimulated whole salivary secretion rate is determined, and the buffering capacity is assessed. For a subgroup of participants, saliva composition (proteins, ions, metabolites and inflammatory biomarkers) and the oral microbiome will be analysed.

Register data will be obtained from the National Board of Health and Welfare (National Prescribed Drug Register, National Register of Care and Social Services for the Elderly and Persons with Impairments, National Register of Interventions in Municipal Health Care, National Cause of Death Register, National Patient Register, National Dental Health Register) and from the Swedish Social Insurance Agency (Micro Data for Analysis of Social Insurance [MiDAS] database, Dental care). Register data on healthcare utilisation will also be obtained for a subgroup of patients. Register linkage will be performed using personal identity numbers, and the data will be pseudonymised after data collection.

The collected register data will cover the period from one year prior to diagnosis to five years after the completion of treatment, and will include information about, for example, prescribed drugs, municipal health and social care, specialised outpatient and inpatient care, registered sickness absence, and costs related to functional impairments, as well as dental healthcare.

##### Data security

Data are collected using a secure, web-based platform (REDCap) designed to create and manage research databases [25]. REDCap is also used for randomisation. The system supports validated data entry, audit trails, automated export to statistical software, and advanced features for longitudinal data collection and multi-site collaboration. Confidentiality is ensured by using coding lists with limited access. All data handling is compliant with the European Union General Data Protection Regulation (GDPR, 2016/679).

### Feasibility testing

The feasibility of the intervention will be tested after the 6-month follow-up, once participants have been randomised. The first randomised participants will be asked to take part in the feasibility testing. We will use individual and/or focus group interviews with a sample of participants (*n* = 10) and also with a subgroup of healthcare providers responsible for recruiting participants to the study and conducting the data collection and intervention (dental hygienists, clinical/research nurses, *n* = 10). Interviews will follow a semi-structured format based on a predefined guide. The aim is to explore the feasibility and acceptability of the data collection procedures for primary and secondary outcome measures, as well as the intervention itself [33]. Additionally, we will review recruitment and retention rates, completeness of outcome measure data, and practical aspects of data collection. Protocol modifications will be implemented if suggested by the feasibility testing results. Data from the HNC survivors participating in the feasibility testing will be included in the final analysis, provided that any adjustments to the oral health care programme do not compromise the study’s integrity.

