### Data processing and analysis

The effects of the intervention will be evaluated in comparison with standard of care. Outcomes will be analysed using either change‑from‑baseline or end‑point values, depending on the nature of each variable. Time‑to‑event outcomes, where applicable, will use time from randomisation to the occurrence of the event of interest.

The main statistical analyses will be performed by statisticians according to the intention-to-treat (ITT) principle. The primary analysis of the EORTC QLQ-HN43 [27] will be conducted using an ANCOVA model adjusting for baseline values, with robust standard errors. Analyses will be performed at each follow-up time point, with the primary comparison at 12 months. To account for within-subject correlation, a linear mixed-effects model with random subject intercepts and a treatment-by-time interaction, using all three follow-up time points, will be used as a sensitivity analysis.

Missing data will be addressed using multiple imputation under the assumption that data are missing at random. Effect size will be estimated using Cohen’s d. Sensitivity analyses to assess the impact of non-compliance will include complete-case and per-protocol analyses. Descriptive statistics will be presented as numbers and percentages for categorical variables, and as means with standard deviation (SD) for continuous variables.

Resource use and societal costs will be used to investigate cost-effectiveness. The economic evaluation will be based on the direct medical costs of specialised healthcare (calculated from diagnosis-related group weights) and drug costs (the register includes costs for dispensed prescription drugs) among HNC survivors, as well as the direct non-medical costs of formal assistance services (assistance and home care, costed using templates from national and municipal statistics), costs for dental care, and indirect costs in the form of productivity loss for sickness absence, estimated according to the human capital approach. A subgroup analysis will be conducted using administrative data on primary care use from one healthcare region and unit costs for such use from national statistics, to identify the effect of including primary care in the evaluation. The economic evaluation will estimate societal costs over a one-year time horizon for each patient; no discounting will therefore be necessary in these analyses. Societal costs will be reported, as well as costs by components and payers.

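### Conditional inclusion of already-randomised feasibility participants in the final analysis is not reconciled with the unqualified intention-to-treat statement

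*Protocol article*

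**What the plan says.** Three statements in the Feasibility testing section of the protocol article belong together.

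- Timing: feasibility "will be tested after the 6-month follow-up, once participants have been randomised".
- Who is approached: "The first randomised participants will be asked to take part in the feasibility testing". The method is "individual and/or focus group interviews with a sample of participants", with n = 10, plus 10 healthcare providers.
- Consequence: "Protocol modifications will be implemented if suggested by the feasibility testing results". The data of the cancer survivors who took part "will be included in the final analysis, provided that any adjustments to the oral health care programme do not compromise" the integrity of the study.

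The Data processing and analysis section then states: "The main statistical analyses will be performed by statisticians according to the intention-to-treat (ITT) principle". It adds complete-case and per-protocol analyses as sensitivity analyses for non-compliance. It does not mention feasibility participants when it defines the main analyses.

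**The concern.** The feasibility participants are not an external pilot. They are the first patients randomised in the trial itself, so an ITT analysis has to count them in the arm to which they were assigned. The proviso leaves room to take them out later, depending on how a programme change is judged. The two sections therefore describe different main analysis sets whenever the proviso is used.

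The comparability of the arms is at stake. Randomisation protects the comparison only if membership of the analysis set is fixed by randomisation and not by something decided or done afterwards. The trigger is not remote, because the plan expects to act on the feasibility results if they suggest changes.

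**Working it through.** **1. The passages side by side**

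| Question | Feasibility testing | Data processing and analysis |
|---|---|---|
| Are these patients randomised? | Yes, before feasibility testing starts | ITT covers those randomised |
| Are they in the main analysis? | Yes, unless programme adjustments compromise integrity | Yes, no exception given |
| When is this settled? | After randomisation, once adjustments are known | At randomisation |

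The clause refers to the final analysis. It cannot be read as one of the listed sensitivity analyses, because those are complete-case and per-protocol and are tied to non-compliance. The conflict is therefore with the main analysis.

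**2. Does the proviso reach its own target?**

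Its evident purpose is to protect the result from data collected under a superseded programme version. Suppose it applies to interviewees only. Patients assigned to the intervention at the same time, under the same early version, but not interviewed would stay in. An interviewed standard-of-care patient, who is not offered the programme, could be removed. Exposure to the early version follows date and arm, not interview participation.

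**3. Size**

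Inputs from the Participants section: 300 to be randomised, 250 (125 per group) for the power calculation, difference 10, SD 33, two-sided 5%, zero baseline correlation. Input from the Feasibility testing section: 10 participants interviewed.

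- Plan's own step from 250 to 300: implied loss 1 − 250/300 = 16.7%, and 250/(1 − 1/6) = 300. This reproduces.
- Share at stake if the clause means the 10 interviewees: 10/300 = 3.3% of those randomised, or 10/250 = 4.0% if all 10 would otherwise be evaluable.
- Power by the normal formula, Φ(10/(33·√(1/n₁ + 1/n₂)) − 1.96):
  - 125 and 125: 66.9%
  - 120 and 120: 65.1%
  - 115 and 125: 65.0%

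The loss is about 2 percentage points however the 10 are split. The starting level of 66.9% is not the plan's approximately 80%. That figure comes from a simulation whose outcome distribution is not shown. The gap is a separate matter, and only the difference is used here.

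**4. Possible shift in the estimate (illustration)**

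Suppose the 10 have a mean outcome D units away from the mean of their arm.

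- All 10 from one arm of 125: removal moves that arm's mean by 10·D/115. D = 10 gives 0.9 units; D = 33 (one SD) gives 2.9 units. The target difference is 10.
- Five from each arm with the same D: each mean moves by 5·D/120, and the shifts cancel in the comparison.

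Both D and the split are assumptions. The documents give neither.

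**The case against.** The best defence is that the default is inclusion. Exclusion arises only if a programme adjustment compromises integrity, and that may never happen. This stands: ITT is breached only if the proviso is used. It does not remove the conflict, because the text reserves the option and the ITT statement does not allow for it.

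A second defence concerns who is meant. Feasibility testing is wider than the interviews: "we will review recruitment and retention rates, completeness of outcome measure data, and practical aspects of data collection". The analysis section also speaks of quantitative data from a feasibility trial. The clause could therefore mean an early cohort in both arms, excluded by calendar time. This also stands as a possible reading. On it, the mismatch in step 2 and the 3.3% fall away. A departure from ITT in the main analysis would remain, for a group of undefined size.

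A reader might also infer three stronger points that the documents do not support:

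- That the interviewees will come mainly from the intervention arm. Neither arm is singled out. The first aim named is the feasibility of data collection, which applies to all participants; the intervention comes second.
- That the decision will be made by people who know allocation or have seen outcomes by arm. No decision-maker is named. The Discussion says only that blinding is not feasible. The items reviewed are recruitment, retention, completeness and practicalities, not outcome values.
- That the lack of a criterion, decision-maker or date is itself an error. An article commonly leaves such detail to the full protocol or analysis plan.

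**Conclusion.** The point holds as a conflict between two stated rules. Already-randomised feasibility participants enter the final analysis subject to a later judgement, while the main analyses are to be "performed by statisticians according to the intention-to-treat (ITT) principle" without exception. It would be wrong to say that ITT is already broken; that would follow only from using the proviso.

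On the assumption that the clause means the 10 interviewees, at most 3.3% of the 300 randomised are affected and about 2 points of power are lost. Any bias depends on an arm split and an outcome difference that are not given; it could be nil or, in the illustrated one-arm cases, 0.9 to 2.9 units. The matter is modest in size but should be corrected, because it concerns who is in the primary analysis and is easily avoided.

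**What to change.** Delete the proviso. State instead that all randomised participants, including those in the feasibility testing, are in the primary ITT analysis in their assigned arm, whatever adjustments are made to the programme.

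If the programme changes materially, record the date of the change. Then run one sensitivity analysis that excludes all participants, in both arms, randomised before that date. This addresses the legitimate worry about an early programme version symmetrically and by calendar time. It works under either reading of who the feasibility participants are.

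The cost is a short text change. The downside is that a few participants who received an early version stay in the primary set, which may dilute the estimated effect slightly.

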### Data processing and analysis

The effects of the intervention will be evaluated in comparison with standard of care. Outcomes will be analysed using either change‑from‑baseline or end‑point values, depending on the nature of each variable. Time‑to‑event outcomes, where applicable, will use time from randomisation to the occurrence of the event of interest.

The main statistical analyses will be performed by statisticians according to the intention-to-treat (ITT) principle. The primary analysis of the EORTC QLQ-HN43 [27] will be conducted using an ANCOVA model adjusting for baseline values, with robust standard errors. Analyses will be performed at each follow-up time point, with the primary comparison at 12 months. To account for within-subject correlation, a linear mixed-effects model with random subject intercepts and a treatment-by-time interaction, using all three follow-up time points, will be used as a sensitivity analysis.

Missing data will be addressed using multiple imputation under the assumption that data are missing at random. Effect size will be estimated using Cohen’s d. Sensitivity analyses to assess the impact of non-compliance will include complete-case and per-protocol analyses. Descriptive statistics will be presented as numbers and percentages for categorical variables, and as means with standard deviation (SD) for continuous variables.

Resource use and societal costs will be used to investigate cost-effectiveness. The economic evaluation will be based on the direct medical costs of specialised healthcare (calculated from diagnosis-related group weights) and drug costs (the register includes costs for dispensed prescription drugs) among HNC survivors, as well as the direct non-medical costs of formal assistance services (assistance and home care, costed using templates from national and municipal statistics), costs for dental care, and indirect costs in the form of productivity loss for sickness absence, estimated according to the human capital approach. A subgroup analysis will be conducted using administrative data on primary care use from one healthcare region and unit costs for such use from national statistics, to identify the effect of including primary care in the evaluation. The economic evaluation will estimate societal costs over a one-year time horizon for each patient; no discounting will therefore be necessary in these analyses. Societal costs will be reported, as well as costs by components and payers.

The economic evaluation will compare differences in costs with differences in health, measured as Quality‑Adjusted Life Years (QALYs), which will be estimated using both the EORTC-30 [26] and the EQ-5D-3 L (Table 1) [29, 30]. Health status will be translated into QALYs using established methods and value sets. Cost-effectiveness will be analysed using methods that can manage skewed cost data and, where necessary, impute missing data. The outcome will be reported as an incremental cost-effectiveness ratio showing the cost of achieving a given health gain, a cost-effectiveness plane illustrating the cost and health components, and cost-effectiveness acceptability curves in cases such as improved health at increased cost. Stochastic and probabilistic sensitivity analyses will be performed to investigate the effects of assumptions made in the analysis, such as price levels for different resources used, the value set for converting health status to QALYs, and heterogeneity within the patient population.

Qualitative data from the feasibility testing will be transcribed verbatim and analysed using thematic analysis [34]. Quantitative data from the feasibility trial will be analysed descriptively to optimise any data collection procedures.

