In accordance with standard clinical practice in Sweden, all patients with HNC scheduled to receive RT are routinely invited to undergo an oral health assessment prior to initiation of cancer treatment. Teeth with extensive periapical disease, moderate to severe attachment loss, or severe decay are extracted, and manifest caries lesions are treated. Conventional periodontal therapy is administered if necessary. Standard of care often includes follow-up at a specialist dental clinic for up to approximately three months after treatment. After this, patients are generally advised to visit their own dental clinic, when dental care costs are typically paid for by the patients themselves. Consequently, oral health follow-up for HNC survivors in Sweden lacks consistency and uniformity, and its frequency is variable across healthcare regions. Many patients are unable to afford dental care or choose not to prioritise it. The lack of support and the financial burden associated with dental care for patients with HNC are increasingly recognised within the research community [20, 21]. To support oral health and facilitate early detection of dental caries, patients with HNC should receive a comprehensive oral health care plan with frequent follow-ups over a long period of time after the completion of cancer treatment.

Well-defined, evidence-based guidelines across the healthcare system, including dental services, are essential to support HNC survivors in managing complex oral health challenges. However, there is currently limited evidence regarding how to implement such strategies effectively. This is, therefore, a protocol for a multicentre two-armed randomised controlled trial (RCT) with the aim of evaluating an oral health care programme designed to prevent or mitigate late oral sequalae following completion of HNC treatment, and assessing its impact on HRQoL, oral health, work ability, nutritional status, psychological well-being, and healthcare-related economic costs. Conducting a RCT to test this programme will provide valuable evidence for how structured, evidence-based interventions can be integrated into survivorship care to preserve oral health and improve long-term outcomes. We hypothesise that a clinically structured programme for HNC survivors will significantly improve both oral health and HRQoL.

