### Participants

Patients diagnosed with HNC are randomly assigned in a 1:1 ratio to either an oral health care programme (intervention) or standard of care. The power analysis was performed based on data from a prospective observational study on HNC (ClinicalTrials.gov NCT03343236) involving individuals with various HNC diagnoses. In that study, we collected data using the European Organisation for Research and Treatment of Cancer Quality of Life Questionnaire – Head and Neck Module (EORTC QLQ-H&N35) [24]. Data from this instrument, specifically the ‘Dry mouth component’ of the EORTC QLQ-H&N35, form the basis for the power calculation, assuming a mean of 52 and a standard deviation (SD) of 33 after one year in the standard of care group.

Sample size was determined using simulation-based power calculations for an ANCOVA model, adjusting for baseline values, with robust standard errors. Simulations enable a skewed outcome bounded between 0 and 100 and a conservative zero correlation between baseline and follow-up. Simulation-based power calculations were chosen due to the discrete and bounded nature of the outcome variable, which violates the assumptions underlying standard normal-theory sample size formulas.

A total of 250 participants (125 per group) provides approximately 80% power to detect a clinically relevant difference of 10 units between groups at a two-sided 5% significance level. To account for potential dropouts, we plan to enrol 300 patients in total that will be randomised. Calculations were performed using R version 4.3.3.

Inclusion started in September 2025. Patients are recruited at different hospitals in Sweden. Clinical/research nurses at each cite identify eligible patients in relation to a multidisciplinary conference, where treatment options for newly diagnosed patients with HNC are discussed and planned. Informed consent is obtained from the participant by the clinical/research nurses. The number of patients who decline participation or who are inadvertently omitted from being approached is documented in the research database Research Electronic Data Capture (REDCap) [25].

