There are important methodological considerations that need to be acknowledged. Given the study design and intervention, blinding will not be feasible. This will pose a particular challenge regarding the PROMs [39]. When an intervention is delivered through direct human interaction, there is an inherent risk that attention bias will affect PROMs. Hence, improvements in PROM scores may not solely reflect the intervention itself but could also result from increased frequency of patient–provider contact. Additionally, patients who are aware of receiving an intervention may report improvements more positively. When using PROMs, there is a risk that patients may adapt to their condition or treatment sequelae, leading to changes in PROM scores that reflect adaption rather than true changes in symptoms. We believe that using PROM instruments will add substantial value and enable us to demonstrate the therapeutic benefit of the oral health care programme from the patient’s perspective. To address the previously described potential biases associated with using PROMs, and to add objectivity, the outcomes measured are not based solely on PROMs but instead on a combination of patient-reported outcomes, clinical indicators, imaging, and biochemical biomarkers.

The extensive data collection is a strength and will enable us to investigate the longitudinal impact of the oral health care programme. To enhance the generalizability of the findings, a diverse and inclusive cohort of patients with HNC, representing different tumour sites, stages, and treatment modalities, will be recruited. We will use REDCap [25] for randomisation, which enables instant and consistent allocation according to a predefined scheme, thereby reducing the risk of human error. The planned feasibility study is an additional strength, as it will enable us to resolve methodological issues early and identify where modifications are necessary to strengthen trial methodology and operational processes [33].

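### The primary ANCOVA adjusts only for a pre-treatment score; adding the 6-month randomisation-visit score, tumour site, modality and region would be a cheap gain in precision

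*Protocol article*

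**What the plan says.** Under Data processing and analysis, the Protocol article states that the primary analysis of the EORTC QLQ-HN43 "will be conducted using an ANCOVA model adjusting for baseline values, with robust standard errors", "with the primary comparison at 12 months". The Participants section sizes the trial with the same model, using "simulation-based power calculations for an ANCOVA model, adjusting for baseline values, with robust standard errors", and plans on no correlation between baseline and follow-up, which it describes as conservative.

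Allocation and follow-up defines baseline as a visit ahead of cancer treatment. Randomisation takes place at a separate, later visit, six months after treatment has ended. The Data collection overview lists both visits as occasions when data are collected from everyone.

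The same overview records "tumour site and stage, treatment modality, comorbidities and medication". The trial is multicentre. The Background says of usual oral follow-up that "its frequency is variable across healthcare regions". The Discussion describes the intended cohort as "representing different tumour sites, stages, and treatment modalities". The article names no covariate other than the baseline value for the primary model and describes no stratification factors.

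**The concern.** By the plan's own sample-size assumption, the one covariate in the primary model explains nothing. Cancer treatment, which drives later oral symptoms, falls between that measurement and randomisation. The score at the randomisation visit already carries the effect of that treatment, yet the model does not use it.

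Tumour site, treatment modality and region are also settled before randomisation, and the article gives indirect reasons to expect them to matter:

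- The Background links irradiation of the salivary glands to reduced salivary function, and the powering scale is dry mouth. Eligible tumours run from the oral cavity and salivary glands to advanced larynx, with several treatment combinations, so gland exposure should differ.
- Intervention and standard of care says that a partial dental allowance may be open to patients whose radiotherapy targeted the oral cavity. Access to subsidised care therefore depends partly on the irradiated site.
- Usual follow-up differs between regions, so comparator care may differ too.

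At stake is the width of the interval for the primary comparison. Whatever these factors explain stays in the residual.

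**Working it through.** **Inputs from the Participants section:** SD 33 and mean 52 in the control arm at one year (dry mouth scale of the HN35, the only scale with a stated SD), difference 10 units, 125 per arm, testing "at a two-sided 5% significance level", zero baseline correlation.

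**Assumed, not in the documents:** R² for tumour site, modality and region; correlation r between the 6-month score and the 12-month outcome.

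**1. The plan's own figure.** The article says that 250 patients "provides approximately 80% power to detect a clinically relevant difference of 10 units between groups". With zero correlation the ANCOVA reduces to a two-sample comparison:

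- SE = 33 × √(2/125) = 4.174
- Power = Φ(10/4.174 − 1.960) = Φ(0.436) = 66.8%

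The stated 80% is not reproduced. Simulating the baseline-adjusted ANCOVA with robust standard errors (8,000 runs) gives 67.4% for a four-level 0–100 item and 66.8% for a beta outcome. The article does not give the intervention-arm distribution, so an unstated setting could explain the gap. That is a separate matter. To keep it apart, the table below also starts from the stated 80%, which corresponds to a residual SD of 28.2.

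**2. Added factors with assumed R².** Residual SD = 33 × √(1 − R²). Equivalent total N = 250/(1 − R²).

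| R² | Residual SD | Power | 95% CI half-width | Equivalent N | Power if the stated 80% is taken as the start |
|---|---|---|---|---|---|
| 0 | 33.0 | 66.8% | 8.2 | 250 | 80% |
| 0.05 | 32.2 | 69.1% | 8.0 | 263 | 82% |
| 0.10 | 31.3 | 71.4% | 7.8 | 278 | 84% |
| 0.15 | 30.4 | 73.8% | 7.5 | 294 | 86% |

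**3. Cost if the added terms explain nothing.** With q useless terms the SE grows by about √(247/(247 − q)).

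- q = 3: factor 1.006, power 66.3% (loss about 0.5 points)
- q = 10: factor 1.021, power 65.1% (loss about 2 points)
- q = 20: factor 1.043, power 63.2% (loss about 4 points)

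**4. The 6-month score alone.** Residual SD = 33 × √(1 − r²).

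- r = 0.3: power 70.9%
- r = 0.4: power 74.3%
- r = 0.5: residual SD 28.6, power 79.0%, CI half-width 7.1
- r = 0.6: power 85.0%

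**5. Can the gains be added?** Putting a further 0.05 or 0.10 of total variance on top of r = 0.5 (R² 0.30 or 0.35) gives 81.7% or 84.4%. This supposes that site and modality lose none of their explanatory share once the 6-month score is in the model. Both act before that score is taken and partly through it, so these two figures are optimistic.

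**The case against.** The strongest reply is that baseline-adjusted ANCOVA with robust standard errors is valid under randomisation, matches the model used for the sample size, and breaks no rule, since the article describes no stratification factors to adjust for. A longer covariate list is ordinary SAP content. The first part stands: nothing here is an error. The second part carries less weight, because the article names its primary model, and a later SAP with more covariates would depart from the published one.

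Four stronger readings are tempting and are not supported:

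- A reader might infer that the article itself names centre, site and modality as sources of outcome variation. It does not. The Discussion presents the case mix as a gain in generalisability, and the Background remarks are indirect. Its one explicit statement about factors that belong in the analysis concerns biological and lifestyle factors linked to sex.
- A reader might infer that the extra precision is free. The number of centres is unstated and seven tumour sites are eligible, so a finely divided model could lose power (step 3).
- A reader might infer that uncorrected chance imbalance biases the result. It does not; the interval from the stated model already allows for it.
- A reader might take zero correlation as a prediction. It is a cautious planning value, and the analysis will still gain whatever the pre-treatment score explains.

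One ambiguity also remains. The sensitivity mixed model counts three follow-up occasions, not four, so the authors may intend the 6-month value as the analysis baseline. If so, the largest gain is already in the plan and only site, modality and region are left. The article's sole definition of baseline is the pre-treatment visit.

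**Conclusion.** The point holds as a cheap efficiency improvement. The stated primary model is unbiased but leaves out pre-randomisation information that is already available. For site, modality and region the gain is about 2 to 7 power points if they explain 5% to 15% of the variance, and a loss of about 0.5 to 2 points if 3 to 10 terms explain nothing. The 6-month score is probably the larger part: about 12 points at an assumed r of 0.5 (66.8% to 79.0%). Every R² and r is an assumption, the arithmetic uses the dry mouth SD from the planning data, and the separate gains should not be summed. No single figure for the improvement follows from the documents.

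**What to change.** Before any outcome data are compared by arm, prespecify the primary model as:

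- treatment arm;
- score at the 6-month randomisation visit;
- a few coarse tumour-site groups;
- treatment-modality groups that are exhaustive over the inclusion criteria: radiotherapy alone, radiotherapy with SACT, surgery with radiotherapy, surgery with radiotherapy and SACT, and a defined category for any other eligible combination, such as surgery alone if the criteria admit it;
- region, or centres pooled by a rule set in advance;
- robust standard errors, as now.

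Keep the added terms few, given step 3. Put the same covariates in the multiple-imputation model, and keep the baseline-only ANCOVA as a sensitivity analysis. State explicitly which visit supplies the adjusted score.

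The cost is a change of wording in the analysis plan, a few degrees of freedom, and the need to pool small centres. No new data are collected, and type I error is preserved if the model is fixed in advance.
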